#### Specific aim 2: Identify readily available clinical measurements that are associated with residual femur motion, skin strain, and peak pressure within the socket during dynamic activities

Being able to quantify the parameters of interest in a research setting does not easily translate to clinical application. The purpose of this aim is to correlate our laboratory findings with measurements obtained by conventional clinical assessments. We hypothesize that the following clinical measurements correspond to dynamic in-socket mechanics: (H1) static imaging under different loads will correspond to dynamic residual femur motion, (H2) gait analysis will correspond to dynamic pressure distribution, and (H3) residual limb tissue compliance will correspond to peak skin strain.

#### Specific aim 3: Develop and evaluate an improved socket design and optimization process through the use of a predictive model based upon clinical measurements

In order to generate preliminary evidence on the clinical utility of the findings from aims 1 and 2, we will perform a pilot trial, using new subjects, to compare our data-informed optimization process resulting from aim 2 to the conventional iterative process for selecting a socket design and then optimizing the socket fit and function. We hypothesize that the data-informed method is advantageous in terms of (H1) patient-reported outcomes and (H2) cost, defined by the number of visits and socket iterations, and the amount of labor required to optimize the socket fit and function.

### Trial design {8}

The trial design is an exploratory single-group crossover trial (Fig. 6).

**Fig. 6 Fig6:**
[figure not shown]
Flowchart showing the relationship between aims 1 and 2 (green background) and the pilot clinical trial, aim 3 (orange background). As an example, the flowchart shows three clinical measurements identified in aim 2 that correlate to in-socket mechanics obtained from research-grade measurements. In this example, those three clinical measures will then be used as predictors to guide the quantitative socket design

## Methods: participants, interventions, and outcomes

### Study setting {9}

The study will be conducted at the Biodynamics Laboratory, an academic research laboratory within the University of Pittsburgh. Participants will be recruited from the local limb loss population.

### Eligibility criteria {10}

We aim to work with a representative, yet homogeneous sample of transfemoral amputees. All prosthesis users will have been ambulating with a prosthetic for at least 1 year. All participants will be under 125 kg of body weight. The amputation risk in males is 1.7 (dysvascular) to 4.9 (traumatic) times greater than in females [32], and our sample is assumed to be representative of that distribution. A weight limit of 125 kg is typical for most standard prosthesis componentry. Participants will be between 18 and 80 years of age and must be able to walk unassisted on a treadmill. Pregnant women will be excluded from the data collection to avoid the risk of exposure to ionizing radiation. An additional inclusion criterion for the participants in the pilot clinical trial is that they will be in need of a new socket.

The cause of limb loss will not be considered as an inclusion criterion, as the principal mechanisms under investigation apply irrespectively of the amputation cause. It may be possible to investigate any differences by etiology in post hoc analysis. Likewise, the residual limb length will not be considered as an inclusion criterion but will be documented and analyzed as appropriate post hoc.

### Who will take informed consent? {26a}

Participants’ informed written consent will be obtained by the study PI, [name], or the study coordinator.

### Additional consent provisions for collection and use of participant data and biological specimens {26b}

Not applicable as this trial does not involve collecting biological specimens.

### Interventions

#### Explanation for the choice of comparators {6b}

Every participant in aims 1 and 2 will be fitted with several different check-sockets for this study, each deliberately modifying one of the independent variables: brim height, volume, cross-sectional geometry, and material stiffness. These variables are known to have an effect on the comfort and function of the socket, and they are among those routinely altered in the static and dynamic fitting process [33]. Those modifications are generally iterative and performed in conjunction with others. For instance, changes in the geometry such as the oblique medio-lateral dimension at the perineum by padding the area of the ischial containment level will also affect the volume of the socket as well as the material stiffness in the modified region. The degree of modifications and manner of combinations is very much customized and informed by individual characteristics such as soft tissue content and pain tolerance. For the study, in order to standardize interventions as much as possible and minimize the risk of drastically compromised socket fit, we will make well-defined modest changes using the participants’ original (current) sockets as the baseline. One single prosthetist will facilitate all the modifications to assure consistency across the sample.

#### Intervention description {11a}

For all aims, we will start with a shape capture of the existing socket. From that scan, a positive model will be generated that will enable the fabrication of check sockets. Six to eight such check sockets will be produced for each participant as detailed below, using industrial service fabrication, where applicable, to make the variants. This will result in consistent socket quality across sockets and across participants.

##### Modified stiffness

Two check sockets based on the original positive model will be fabricated using different materials that represent different stiffness grades [34]: polyethylene terephthalate glycol (PETG), sold as Vivak®, and ethylene vinyl acetate (EVA), sold as ThermoLyn Soft®. Both material types are routinely used in clinical prosthetics, where the stiffer PETG material is preferred for check socket fittings and the softer EVA material for definitive sockets (where long-term dimensional stability can be supported by an additional laminated container socket).

##### Modified brim height

The PETG copy of the participants’ existing socket can be modified by grinding down the material to a desired lower brim height. Assuming that the socket fits well, there is generally no clinical rationale for raising the brim height because it would worsen both fit/function and comfort. Instead, the brim height will be reduced in two stages, by 5 and 10% of the overall socket length. Lowering the brim height (up to a certain point) will, by trend, increase wear comfort and hip range of motion but decrease suspension and weight-bearing ability. Depending on the randomization schedule for an individual participant, not all two versions of the socket with the lower brims will have to be fabricated, but the initial socket from above will be modifiable between tests to represent one or both of the other intervention levels.

##### Modified volume

Next, two derivative sockets will be fabricated (from PETG material) that are 6% oversized and undersized, by globally altering the model volume in accordance with established methods. Volume reductions of up to 6% from the original cast model are commonly undertaken in clinical prosthetics and are informed by the soft tissue content of the residual limb [17].

##### Modified cross-sectional geometry

Much like the socket volume reduction will be influenced by the tissue composition of the residual limb, the degree to which the socket geometry re-shapes the uncompressed limb will vary between patients. This can be illustrated when considering the differences between the classic ischial containment socket, termed Contoured Adducted Trochanteric-Controlled Alignment Method (CAT-CAM) by Sabolich [35], and the more recent Marlo Anatomical Socket (MAS), proposed by Ortiz [36] (Fig. 7). For the study, the original socket model of each participant will be the basis for two modifications of the cross-sectional geometry toward the opposite ends of the spectrum. Inevitably, the degree to which those modifications are possible without interfering with the usability of the socket is subject to individual differences and will be determined by the study prosthetist accordingly.

**Fig. 7 Fig7:**
[figure not shown]
Illustration of geometry modifications. The CAT-CAM socket on the left follows widely the limb anatomy; the MAS socket on the right is more aggressive in defining the limb shape (adapted from Psonak, Richard. “Transfemoral prostheses” in orthotics and prosthetics in rehabilitation, Oxford, Elsevier, 2^nd^ Edition, 2007: 652-684)

#### Criteria for discontinuing or modifying allocated interventions {11b}

Socket comfort will be routinely monitored as part of the outcome assessment during the intervention periods. Any adverse effects will be recorded, reported, and evaluated in correspondence with applicable rules. In the event that it is determined that an observed adverse event is attributable to the intervention (and not a unique response/unique circumstances in the individual case), this intervention will be discontinued or modified to address the issue for this and subsequent data collection sessions.

#### Strategies to improve adherence to interventions {11c}

For aims 1 and 2, interventions (modified check sockets) will be administered only during data collection sessions in the lab. Study personnel will be present throughout those periods to respond to or prevent any issues, including a lack of adherence (i.e., participants doffing the socket during the test).

For aim 3, participants will be fitted with a new socket that will replace their original one on their regular prosthesis. The original socket will be retained at the prosthetist’s office to prevent unauthorized switching back by the participant or others. Participants will be asked to not use other prostheses they may own during the study period, and adherence to this will be evaluated by exit interviews.

#### Relevant concomitant care permitted or prohibited during the trial {11d}

There are no interactions between the intervention and any concomitant care or interventions. Participants will be encouraged to make no adjustments to their normal routine while in the data collection protocol.

#### Provisions for post-trial care {30}

Participants will be able to follow up with their prosthetist, who is part of the study team, as part of their continued routine prosthetic care. Any long-term harms from participation can be assessed during these appointments. Due to the nature of the intervention (prosthetic socket modifications comparable to routine clinical care interventions), no long-term adverse effects are anticipated.

### Outcomes {12}

Outcomes for each participant will be averaged across three trials for each of the interventions, to analyze the change from baseline with different socket designs.

Many of the assessment methods are identical or equivalent to clinical assessment instruments that are associated with high validity and low risk for the target population. The effective radiation dose due to dynamic biplane radiography is estimated to be 2.0 mSv or less for the 27 trials collected for each participant. For comparison, the average effective dose associated with a knee CT scan from our previous studies was 1.4 mSv, and in the USA, we receive about 3.0 mSv of exposure from natural background radiation every year [37].

The following is the primary outcome variable:
*Socket comfort*

The following are the secondary outcome variables:
*Hip range of motion (ROM)**Three-dimensional (3D) skin motion within the socket**Residual femur position within each socket**In-socket pressure**Plantar pressure**Ground reaction forces during gait**Overall body motion (e.g., trunk lean, hip flexion/extension) during gait*

#### Participant timeline {13}

Participants in the first stage (aims 1 and 2) of the study, upon eligibility screening and completing the consent process, will be fitted for a check socket. After 4 weeks, during which time 8 derivatives of the socket will be produced, participants will complete testing with each of those socket variants over one or two lab visits. The participant timeline for the second stage (aim 3) includes clinical testing of one socket variant and spans a larger period (Fig. 8).

**Fig. 8 Fig8:**
[figure not shown]
Schedule of enrollment, interventions, and assessments

#### Sample size {14}

To facilitate aims 1 and 2, GLM will be utilized, which is a flexible generalization of ordinary linear regression that allows for response variables that have error distribution models other than a normal distribution and is often robust to smaller sample sizes. With a sample size of *n* = 30 at 80% power and *α* = .05, we should be able to detect a moderate-to-large overall model effect (*f*^2^ = 0.45), while including all three in-socket mechanics. We will examine the effect(s) of each in-socket mechanical parameter on outcomes by utilizing the type III sum of squares tables. If our sample size drops below 30, we will develop separate models for each of the parameters of interest and outcome.

For aim 3, in order to compare the two methods of socket design (the quantitative design method compared to standard of care), we will compare patient-reported outcomes and cost between the two methods, utilizing the Wilcoxon-Mann-Whitney non-parametric test. With a sample size of *n* = 15 at 80% power and *α* = .05, we will be adequately powered to detect a moderate-to-large effect (*d* = 0.476) with respect to the differences in patient-reported outcomes and cost by method.

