## Statistical methods

### Statistical methods for primary and secondary outcomes {20a}

#### Aim 1

The effects of in-socket mechanics, such as residual bone motion, peak skin strain, and pressure distribution on both physical function and patient-reported outcomes will be assessed using a generalized linear model (GLM). We will examine the effect(s) of each in-socket mechanical parameter on outcomes by utilizing the type III sum of squares tables. If our sample size drops below 30, we will develop separate models for each of the parameters of interest and outcome. Finally, we will create a unified model, containing the statistically significant parameter coefficients, which will allow us to predict physical function and patient response based on the changes to the included parameter estimates.

#### Aim 2

We will use partial correlation to examine the association between residual femur motion, skin strain, pressure, and readily available clinical measurements, while adjusting for potential confounders such as residual femur length (derived from CT data), overall residual limb length (measured from ischial tuber to distal end of the limb by caliper), contraction potential (tape measured as the difference of circumferential volumes during thigh muscle contraction and relaxation), and soft-tissue coverage (measured as a ratio between thigh and femur diameter). Partial correlation is a measure of the strength and direction of a linear relationship between two continuous variables whilst controlling for the effect of one or more other continuous variables (also known as “covariates” or “control” variables). Although partial correlation does not make the distinction between independent and dependent variables, the two variables are often considered in such a manner (i.e., you have one continuous dependent variable and one continuous independent variable, as well as one or more continuous control variables). If data is not approximately normal, we will use log transformations. Moderate-to-strong, significant correlations between research-grade and clinical data will be retained for empirical testing in aim 3.

#### Aim 3

Statistical analysis for aim 3 will involve two parts. First, the predictive model developed in aims 1 and 2 will be tested using data from 15 new participants (i.e., data not used to create the model). Second, we will compare the quantitative socket design to the current standard of care, in terms of patient outcomes and cost.

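### The 80% power stated for aims 1 and 2 together belongs to a three-predictor GLM; aim 2 uses partial correlation with a significance gate, for which the stated power does not hold

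*Protocol article*

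**What the plan says.** Sample size {14} covers the first two aims in one paragraph. It opens "To facilitate aims 1 and 2, GLM will be utilized, which is a flexible generalization of ordinary linear regression". Its power statement takes 30 participants, 80% power and a .05 level, and claims enough sensitivity to "detect a moderate-to-large overall model effect (*f*^2^ = 0.45), while including all three in-socket mechanics". No other power statement is given for aim 2.

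Statistical methods {20a}, Aim 2, names a different analysis: "We will use partial correlation to examine the association between residual femur motion, skin strain, pressure, and readily available clinical measurements". Four covariates are named for the adjustment (femur length, limb length, contraction potential and soft-tissue coverage), and the list is left open. The abstract also assigns the GLM to aim 1 and partial correlation to aim 2.

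The Aim 2 text ends with a selection rule: "Moderate-to-strong, significant correlations between research-grade and clinical data will be retained for empirical testing in aim 3". Neither boundary of moderate or strong is given as a number.

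**The concern.** The model in the sample size paragraph cannot be the aim 2 analysis. Its three predictors are the in-socket mechanics and its responses are comfort and function. In aim 2 the in-socket mechanics are themselves one side of each correlation, and the clinical measurements are the other side. A reader of Sample size {14} would nevertheless take 80% power as covering both aims.

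This matters because the aim 2 rule decides which clinical measurements reach the aim 3 design process, and significance is one of its two conditions. If power for that condition is well below 80% at correlations the investigators would call moderate, a measure may fail the rule because of the sample size. The article gives the reader no way to see this. The paragraph's fallback for fewer than 30 participants, separate models per parameter, also addresses only the GLM.

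**Working it through.** **1. The plan's own figure.** Inputs from Sample size {14}: n = 30, α = .05, f² = 0.45, u = 3 predictors. Overall F test with u = 3 and v = 30 − 3 − 1 = 26 df, noncentrality λ = f²·n = 0.45 × 30 = 13.5. Power is 82.7%; the smallest n giving 80% is 29, and the smallest f² giving 80% at n = 30 is 0.42. With the more conservative λ = f²·v, power is 76.4%. The printed figure therefore reproduces for a three-predictor model, which is the aim 1 analysis.

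**2. The aim 2 gate.** Inputs: n = 30 (Sample size {14}); k = 4 named covariates ({20a}, Aim 2); two-sided .05 and one independent value per participant (both assumed, as the article states neither for aim 2).

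- Degrees of freedom: n − k − 2 = 30 − 4 − 2 = 24.
- Critical t = 2.064, so critical |r| = t/√(df + t²) = 2.064/√(24 + 4.26) = 0.388.

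**3. Power of the gate.** Fisher z: power ≈ 1 − Φ(1.96 − √(n − k − 3)·atanh r), with √23 = 4.796. The right-hand column is a simulation of the exact t test on 24 df (100,000 replicates).

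| True partial r | 4.796 × atanh r | Power, Fisher z | Power, simulated |
|---|---|---|---|
| 0.30 | 1.484 | 32% | 33% |
| 0.40 | 2.032 | 53% | 54% |
| 0.50 | 2.634 | 75% | 77% |

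The range 0.3 to 0.5 is an assumption, since the article does not define moderate.

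**4. Detectable correlation at 80% power.** atanh r = (1.960 + 0.842)/4.796 = 0.584, so r = 0.526. The exact test reaches 80% slightly earlier (simulated power 81% at r = 0.52). Hence about 0.52 to 0.53.

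**5. Sensitivity to the assumptions.**

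- No covariates: critical |r| is 0.361, power 36% at r = 0.3 and about 60% at r = 0.4, and 80% power at r = 0.49.
- One-sided test, four covariates: 44% at r = 0.3 and 65% at r = 0.4.
- All nine sockets per participant used (30 × 9 = 270 rows), with an illustrative design effect of 1 + 8·ICC: at ICC 0.5 the effective n is 270/5 = 54, with power 56% at r = 0.3 and 83% at r = 0.4; at ICC 0.8 it is 270/7.4 = 36.5, with 39% and 63%.
- A purely within-participant correlation (30 × 8 − 1 = 239 df): over 99% at r = 0.3.

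The ICC values are illustrations; the article gives none.

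**The case against.** The strongest reply is that the opening phrase is loose, the rest of the paragraph plainly describes aim 1, and its arithmetic is right. A condensed article may leave an aim 2 power figure to the full protocol. That reply stands in part: nothing is miscalculated, and a missing aim 2 figure alone would not be a point. But the article does not merely omit the figure. It says the GLM serves aim 2, which its own methods section contradicts.

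A second reply concerns the unit of analysis, and it stands as a limit on the numbers. Static radiographs, plantar pressure and body kinematics are collected for each socket, as are femur motion and in-socket pressure. If the correlations use those rows properly, power could be clearly higher. One value per participant fits participant-level measures such as tissue stiffness, the clinical measure in hypothesis H3 of aim 2. It is also the n = 30 unit of the sample size paragraph. The article describes no repeated-measures correlation.

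Third, the only effect that the article puts a number on for these aims is f² = 0.45. Read as a single partial correlation it is √(0.45/1.45) = 0.557, for which the aim 2 gate has about 85% power. So for correlations that large the rule is adequately powered.

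A reader might infer that useful clinical measures are likely to be discarded. The documents do not support that. It fits a true correlation of 0.3 (about 67% missed), but not 0.4 (about 46% missed) or 0.5 (about 23% to 25% missed), and it depends on the unit of analysis. Nor is the moderate band out of reach, since observed values from 0.39 upwards pass. A reader might also infer that the significance condition should be dropped for an estimate-and-threshold rule. In a trial described as exploratory, with aim 3 testing the model and the aim 2 correlations on 15 new participants, that is a preference and not a correction.

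**Conclusion.** The point holds in limited form. Sample size {14} names the wrong method for aim 2, and its 80% power applies to aim 1 only. For the written aim 2 rule, power is about 32%, 54% and 77% at true partial correlations of 0.3, 0.4 and 0.5, and 80% only from about 0.52 to 0.53. These figures assume 30 participants with one value each, exactly four covariates, a two-sided .05 test, and 0.3 to 0.5 as the meaning of moderate. Further covariates or dropout would lower them; valid use of per-socket data could raise them. The contradiction between the two sections does not depend on any of these assumptions.

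**What to change.** In Sample size {14}:

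- Limit the GLM sentence and its f² = 0.45 power figure to aim 1.
- Name partial correlation as the aim 2 method.
- State the aim 2 detectable partial correlation together with its unit of analysis: about 0.52 to 0.53 at 80% power with one value per participant and four covariates. If per-socket rows are to be used for some measures, say so, say how clustering within participant is handled, and give the detectable value for that analysis separately.

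In Statistical methods {20a}, Aim 2, add that a measure not retained has not been shown to be unassociated with in-socket mechanics.

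The cost is a less favourable stated detectable effect for aim 2. No participants or measurements are added.

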As part of the pilot clinical trial, we will use empirical data to test the socket modification model(s) created in aim 1 and clinical measure correlations obtained in aim 2. When empirical data are used to evaluate the model, there are several conventional statistical tests that can be applied to test the null hypothesis that the model output is wrong. These involve showing that some form of the predicted value does not equal the same form of the observed value (e.g., typical predicted, typical observed). The simplest empirical comparison is that of a regression of observed values on predicted values. We will obtain data as described for aims 1 and 2 on an additional 15 transfemoral prosthesis users using their current sockets and the sockets designed as part of the standard of care and through the new quantitative design process.

In order to compare the two methods of socket design (the quantitative design method compared to Standard of Care), we will compare patient-reported outcomes and cost between the two methods, utilizing the Wilcoxon-Mann-Whitney non-parametric test. Socket Comfort Scores (SCS, a simple patient-reported comfort score from 0 to 10) will be used to evaluate patient outcomes after wearing the two sockets. The SCS are reported to have a standard deviation of 2.3 points [50], meaning we will be powered to detect a difference of 1.1 points in the SCS given our sample size. With regard to costs, we will compare the two design approaches on the number of visits, cost of materials, and total cost of labor needed to develop the new socket. These costs will be recorded by the study prosthetist in his practice for the standard of care and in the Biodynamics Lab for the quantitative design method.

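### Aim 3: 15 participants do not give 80% power for d = 0.476 (1.1 SCS points); power is about 13–39% two-sided or 21–53% one-sided, depending on the design

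*Protocol article*

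**What the plan says.** Sample size {14} in the protocol article covers both patient-reported outcomes and cost in aim 3. It names the test, "utilizing the Wilcoxon-Mann-Whitney non-parametric test", then states "With a sample size of *n* = 15 at 80% power and *α* = .05" and concludes "we will be adequately powered to detect a moderate-to-large effect (*d* = 0.476"). It does not say whether alpha is one- or two-sided.

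The Aim 3 part of Statistical methods {20a} puts the claim into points: "The SCS are reported to have a standard deviation of 2.3 points", and therefore "we will be powered to detect a difference of 1.1 points in the SCS given our sample size". The same section fixes the number of people: "the predictive model developed in aims 1 and 2 will be tested using data from 15 new participants".

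On whether the comparison is within or between people, the article points two ways. Statistical methods {20a} has data collected on these 15 people "using their current sockets and the sockets designed as part of the standard of care and through the new quantitative design process", and Implementation {16c} says that participants in either phase receive every intervention of that phase in random order. Participant timeline {13}, however, describes the aim 3 stage as clinical testing of a single socket variant.

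**The concern.** An effect just under half a standard deviation is small for 15 people. Even an ordinary two-sided paired t-test on 15 pairs needs a standardized difference of about 0.78 for 80% power, and an unpaired rank test needs more. The named test is the unpaired one, although the fuller description of aim 3 is within-subject.

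This statement is the only sample size justification for aim 3, and it appears in two sections. If it is wrong, readers will credit the pilot with a sensitivity to comfort and cost differences that it lacks, and a non-significant result will look more informative than it is.

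**Working it through.** **Inputs from the protocol article.** n = 15, power 80%, alpha .05, d = 0.476 (Sample size {14}); SCS standard deviation 2.3 and detectable difference 1.1 points (Statistical methods {20a}, Aim 3). Sidedness, within-person correlation and the standard deviation of differences are not given, so I vary them.

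**The plan's own conversion.** 0.476 × 2.3 = 1.095, or 1.1 points. The points figure is thus d multiplied by the quoted standard deviation. This step reproduces; the power behind d does not.

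**Method.** Noncentral t, with the sample size multiplied by the asymptotic relative efficiency 3/π = 0.955 for the rank tests.
- Pairs: noncentrality = d × √(0.955 n), df = 0.955 n − 1.
- Two groups: noncentrality = d × √(0.955 n₁n₂/(n₁+n₂)), df = 0.955(n₁+n₂) − 2.

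**Power at d = 0.476, alpha .05.**

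| Reading of n = 15 | Noncentrality | Two-sided | One-sided |
|---|---|---|---|
| 15 pairs, signed-rank | 1.80 | 38.7% | 52.6% |
| 15 per group, Mann-Whitney | 1.27 | 23.3% | 34.3% |
| 15 in total (7/8), Mann-Whitney | 0.90 | 13.2% | 21.3% |

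Simulation with normal data gives 38.9%, 20.8% and 10.6% two-sided, and 51.9%, 33.5% and 19.2% one-sided. The shortfall does not come from the approximation.

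**Detectable standardized effect at 80% power.**

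| Reading | Two-sided | One-sided |
|---|---|---|
| 15 pairs | 0.80 | 0.69 |
| 15 per group | 1.09 | 0.95 |
| 7/8 | 1.61 | 1.40 |

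For d = 0.476 at 80% power, two-sided, about 39 pairs or 74 per group would be needed; one-sided, about 31 pairs or 58 per group.

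**Where 0.476 could come from.** A one-sided signed-rank test on 30 pairs has a detectable effect of 0.4764 under the same method. With a paired t-test it is 0.465, and with the minimum efficiency of 0.864 it is 0.502, so the match depends on the efficiency convention.

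**In SCS points, 15 pairs, two-sided.** If the standard deviation of differences is 2.3: 0.799 × 2.3 = 1.84 points. If 2.3 is instead the between-person standard deviation, the standard deviation of differences is 2.3 × √(2(1−ρ)):
- ρ = 0.3: 2.72, giving 2.2 points
- ρ = 0.5: 2.30, giving 1.8 points
- ρ = 0.7: 1.78, giving 1.4 points

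**Correlation at which the claim would hold.** Set 0.476/√(2(1−ρ)) equal to the detectable paired effect. Two-sided: (0.476/0.799)² = 0.355 = 2(1−ρ), so ρ ≈ 0.82. One-sided: (0.476/0.693)² = 0.472, so ρ ≈ 0.76.

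**The case against.** The strongest defence is the paired one. The fuller description of aim 3 is within-subject, so d could be in units of the SCS standard deviation, with the pairing supplying the missing precision. This stands as far as it goes: a reader might infer that no reading of n = 15 can reach 80%, and that is too absolute. But the defence needs a correlation of about 0.82 two-sided or 0.76 one-sided. The article states none, and the test it names makes no use of pairing.

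Second, the aim 3 hypothesis is directional and sidedness is unstated, so quoting two-sided power alone would be unfair. That is right, and both are given above. One-sided, the best of the three readings is still only 53%.

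Third, a reader might infer that the calculation was run for 30 pairs, perhaps carried over from aims 1 and 2. The numerical match is close, but the article gives neither 30 pairs nor a one-sided test for aim 3, so this origin is inference and the point does not depend on it. Likewise, the article does not say whether 2.3 is a between-person standard deviation or one of differences. It cannot be called the wrong one, only unspecified.

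Finally, aim 3 is a pilot meant to yield preliminary evidence within an exploratory trial. That can justify 15 people with no power claim at all, but not an incorrect one. It does limit the consequences: the article nowhere calls 1.1 points clinically relevant or ties a decision to a null result, so a prediction that a null result will be read as excluding a relevant benefit goes beyond the text.

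**Conclusion.** The aim 3 power statement is wrong as written. At d = 0.476, 15 participants give roughly 13% to 39% power two-sided, or 21% to 53% one-sided, against the stated 80%. The low end is 15 people split into two groups and the high end is 15 pairs. On the most favourable of these readings, the detectable two-sided effect is about 0.80, or about 1.8 SCS points if the standard deviation of differences is 2.3.

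These figures assume approximately normal data and the usual efficiency of the rank tests, and for 15 pairs that d is the standardized paired difference. The 1.4 to 2.2 point range assumes that 2.3 is a between-person standard deviation and that the correlation lies between 0.7 and 0.3. None of this shows that 15 is the wrong size for a pilot; the error is in what the article says 15 can detect.

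**What to change.** Keep n = 15 and make these changes:

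1. Reconcile Participant timeline {13} with Implementation {16c} and Statistical methods {20a}, so that it is clear whether each aim 3 participant uses both designed sockets.
2. If so, name the Wilcoxon signed-rank test in place of Wilcoxon-Mann-Whitney in the Abstract, Sample size {14} and Statistical methods {20a}. This amends the analysis as well as the power figure and should be recorded as such. State the sidedness.
3. Replace the power sentence, for example: *With 15 pairs and two-sided alpha .05, the Wilcoxon signed-rank test has 80% power for a standardized paired difference of about 0.80, corresponding to about 1.8 SCS points if the standard deviation of differences is 2.3 (1.4 to 2.2 points for a within-person correlation of 0.7 to 0.3 if 2.3 is the between-person standard deviation).* If the groups are in fact independent, give a detectable d of about 1.09 (15 per group) or 1.61 (7/8).
4. Remove the 1.1-point claim, and report the pilot comparison as an estimate with a confidence interval.

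The cost is a less favourable stated figure and, if the design is paired, a documented change of test. Recruitment is unaffected.
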